### Theoretical Framework for the Health Information Technology Intervention

The Theory of Planned Behavior, self-regulation, and mindful decision making are the theories used in the intervention to illicit a behavioral change. The direct determinants of behavioral intention are attitude, normative belief, and perceived control. The Theory of Planned Behavior suggests that the determinant of persons’ behavior is their behavioral intent [14]. Patients who hold strong beliefs that a positive outcome will result from a behavior will also have a positive attitude about that behavior. Normative beliefs are heavily dependent on the individuals’ motivation to comply with those around them. Patients also have to perceive control of the situation, making the behavior decision easy to perform.

In our intervention, patients planning what they are going to order at a restaurant will receive a push notification from the mobile app informing them of the low-sodium options at that restaurant. In food selection, the choice has to be within an area individuals perceive as normal. Providing a food choice on a restaurant menu that others would also purchase gives patients a feeling like they are complying with social norms. In addition, patients have to perceive control of the situation, making the behavioral decision easy to perform. In the setting of a push message provided by the mobile app, we present patients with several options to give them control over which food to choose.

The theory of self-regulation suggests that individuals striving to achieve a behavioral goal learn from their successes and failures. This knowledge is then used to develop strategies that can lead to goal attainment. In this theory, self-monitoring refers to individuals’ awareness of their engagement in a targeted behavior. An important factor in self-regulation is self-efficacy [15]. Self-efficacy refers to an individual’s belief in his or her ability to perform a specific behavior [16]. Accurate self-monitoring, feedback, and self-efficacy are essential components of the self-regulation cycle and are critical for lowering sodium intake [15,17-19].

Behavioral change interventions that focus on self-regulation are particularly well suited for automation. Through the use of the intervention, we will assess patients’ top 5 high sodium-containing food selections. These food selections will be embedded in the mobile app, and a daily push notification will prompt patients to document if they have reduced those foods from their diet.

Mindful decision making is key for patients to make positive food choices. Food choice decisions are complex and incorporate a variety of food behaviors [20]. Value negotiations are a component of food choice decisions. People negotiate competing values, prioritizing values to simplify food choice decisions. For example, patients with hypertension may value their health over other values like taste, cost, convenience, and relationships. Limitation and substitution are common strategies in food choice. Some may limit particular foods or ingredients to meet a goal, while others substitute one food for another to meet the same goal. Health IT can provide a behavioral change intervention for food choices. We provide just-in-time messages at a restaurant and the ability to scan items at a grocery store to promote limitation and substitution strategies. These strategies facilitate food choice decisions by making them automated, so values are not necessary for every situation.

### Aim and Hypothesis

The LowSalt4Life Trial will study the effectiveness of a newly developed mobile app that provides mobile phone sensor-based contextual push messages related to following a low-sodium diet. We will randomize patients with hypertension to the mobile app or standard of care for 8 weeks. From baseline to 8-week follow-up, we will assess the impact of the mobile app on the dietary intake of sodium (measured by 24-hour dietary recall and 24-hour urinary sodium excretion) and confidence following a low-sodium diet, measured by the Self-Care Confidence in Following a Low-Sodium Diet Scale (SCFLDS). We hypothesize that the group randomized to the mobile app will demonstrate improvement in these measurements compared with the control group (Table 1).

### General Design

This is a single-center, prospective, open-label designed clinical trial. Recruitment is being performed at the University of Michigan Health System through our patient recruitment platform and recruitment letters to patients that meet our study criteria. Enrolled patients will be randomized to the mobile app or usual care in a 1:1 fashion using the University of Michigan Consulting for Statistics, Computing and Analytics Research randomization tool. Patients randomized to the mobile app will receive a 30-minute training session about the mobile app and be instructed to use the mobile app for 8 weeks. To address the research bias in this unblinded trial, all primary outcomes measured are objective. Some outcomes are not objective and represent a limitation of this research. This study was approved by the University of Michigan Institutional Review Board.

### Study Subjects

We will enroll 50 patients aged >18 years diagnosed with hypertension and on antihypertensive therapy for at least 3 months. Patients will be excluded if they have CKD, heart failure, SBP >180 mm Hg, diastolic blood pressure >110 mm Hg, insulin-requiring diabetes mellitus, or are taking a loop diuretic, corticosteroid, or nonsteroidal anti-inflammatory medication. CKD is defined as known kidney damage (structural or functional abnormalities) or estimated glomerular filtration rate of <60 mL/min/1.73 m^2^ (CKD stage 3, 4, or 5). Initially consented participants will complete the Block Food Frequency Questionnaire (NutritionQuest) [21], and those with the estimated baseline sodium intake <2300 mg/day will be excluded before randomization.

### Intervention

The intervention with the mobile app includes the following 2 parts: (1) just-in-time contextual tailored messages that promote behavioral changes when a patient enters a grocery store and restaurant and (2) the ability to easily scan and search for the foods at grocery stores and restaurants to find options containing lower sodium content.

Just-in-time contextual tailored messages are generated on the basis of a multifaceted system. Initially, participants complete the Block Sodium Screener (NutritionQuest) and survey to assess their confidence in following a low-sodium diet. Users then create alternatives to the top 5 high sodium-containing foods and map these items to locations. In order to properly target messages, we use artificial intelligence algorithms that analyze the changes in mobile phones sensors (including Wi-Fi, Bluetooth, accelerometer, gyroscope, magnetometer, global positioning system). This takes each user’s past, recognizes his or her present context, and predicts future activity. These predictions then alert the mobile app that the user is entering a grocery store or restaurant. Once the mobile app knows the user’s context, the user receives a tailored message based on the context (grocery store or restaurant), their individual top 5 high sodium-containing foods (from the Block Sodium Screener) and their confidence following a low-sodium diet. These messages are delivered by push notifications.

When a user taps on a just-in-time contextual tailored message, the app is opened to the appropriate section for their context, grocery store or restaurant. The grocery store section provides users with the ability to scan Universal Product Codes on food packaging or text search at the grocery store. The mobile app provides feedback on the sodium content of the food using a traffic light signal red (≥480 mg/serving), yellow (≥120 mg/serving to <480 mg/serving), and green (<120 mg/serving) to show consumers, at a glance, whether a product is high, medium, or low in sodium [22-24]. In addition, the app will list lower sodium options in the same food category (Figure 1). In restaurants, users are presented 3 low-sodium meals for that specific restaurant that were curated by the investigators and be able to search the restaurant’s menu with items ordered by the sodium content, lowest to highest.

### Outcomes

The Automated Self-Administered 24-Hour Dietary Recall (ASA24), developed by the National Cancer Institute for dietary research, will be used to estimate the dietary sodium intake during the trial. The ASA24 is an electronic 24-hour recall website that allows patients to self-administer the survey in a user-friendly manner. The ASA24 allows researchers to send the survey at defined intervals and automatically performs a dietary analysis by converting the dietary recall data into nutrient information based on the Food and Nutrient Database for Dietary Studies. In order to provide a detailed interview, the website includes a meal-based quick list, meal gap review, review of forgotten foods, a final review, and a question about whether the day’s intake was usual or not. In this study, we will obtain the sodium content per day from the Food and Nutrient Database for Dietary Studies-based sodium content analysis completed by the ASA24 website. The ASA24 will be administered at week 0 and 8 of the study (see Figure 2 for details of outcomes).

The most widely used method for monitoring the sodium intake is urinary sodium excretion measured by a 24-hour urine collection. Patients will be instructed to collect all urine voids for 24 hours and return them for analysis for sodium excretion. In addition, the 24-hour urine excretion will be collected at baseline and after 8 weeks. This method is not convenient (eg, difficult to perform collections at work), and some participants may have incomplete urine collections. Owing to these challenges, we will also explore other methods to estimate sodium excretion that would be more practical for use in larger trials.

In addition to the gold standard, the first method to estimate the 24-hour urinary sodium excretion is spot morning urine excretion of sodium. The Kawasaki formula will be used to estimate the 24-hour sodium urinary excretion from a fasting morning urine sample [25]. This approach has been proven to provide a valid estimate of the sodium intake in several patient populations and in large-scale epidemiological studies [26]. Participants will be instructed to fast overnight, void in the morning, and provide us with a second morning urine sample on the day of the assessment. This measurement will be assessed at baseline and after 8 weeks of the study.

**Figure 1 figure1:**
[figure not shown]
An example of the grocery store result screen for tomato soup using a traffic light signal.

**Figure 2 figure2:**
[figure not shown]
Summary of outcomes in the trial. ASA24: Automated Self-administered 24-Hour Dietary Recall; FFQ: Food Frequency Questionnaire; SCFLDS: Self-Care Confidence in Following a Low-Sodium Diet Scale.

The second method for estimating the 24-hour urinary sodium excretion is with a spot urine sample using chloride and creatinine dipsticks. The dipstick method has been validated in patients with hypertension and correlates well with the 24-hour urinary sodium excretion (*r*=.86) [27]. The chloride dipstick is used as a surrogate for sodium excretion. The Quantab chloride dipstick (Hach, Loveland, CO, USA) is placed in a container filled less than halfway with urine. The chloride concentration is determined by observation of the change in color from brown to pale on the dipstick, which is the formation of silver chloride. The creatinine dipstick is similar to the chloride dipstick. The MultistixPro-10LS (Bayer, Elkhart, IN, USA) is a dipstick that includes a color pad for creatinine after it is placed in a container filled with urine. The color pad turns from yellow to green to indicate the creatinine concentration. The predicted 24-hour urinary sodium excretion is calculated on the basis of the 24-hour creatinine concentration calculated using sex, weight, race, and age. This model has been validated and correlates highly (*r*=.93) with 24-hour measurements of creatinine [28]. This measurement will be performed at baseline and after weeks 2, 4, 6, and 8.

The SCFLDS will be used to measure patients’ confidence in following a low-sodium diet. It assesses patients’ confidence in the ability to select and prepare low-sodium foods [29]. The tool consists of 7 items with 4 response options per item. The items ask patients to rate their level of confidence reading food labels, choosing low-sodium food during shopping, choosing low-sodium foods at restaurants, cooking low-sodium foods, choosing low-sodium foods at relatives or friends homes, estimating how much sodium they eat each day, and substituting low-sodium foods for high-sodium foods. The 4 response options are assigned a score of 1-4 (1=not confident; 2=somewhat confident; 3=very confident; 4=extremely confident) and then added for each question. Possible scores range from 7 to 28, and the higher score indicates greater confidence. The SCFLDS will be administered at baseline and after week 8 of the study.

Mobile device analytics will be collected to determine the extent to which the mobile app was used. This outcome will be key in determining the frequency and intensity of the intervention. After a participant receives a push notification on entry to a grocery store and restaurant, we will provide them with a push notification on exit asking them if they chose any of our alternative options. We will also collect any scanned items to understand better the specific foods that participants are seeking more information about. Blood pressure will be monitored on a weekly basis by patients, and the results will be entered into the mobile app and graphically represented.

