**Methods:**

In this single-center, prospective, open-label study, patients will be randomized to a mobile app or usual care for 8 weeks. We will randomize 50 patients (age>18 years) diagnosed with hypertension and on antihypertensive therapy for at least 3 months in a 1:1 manner stratified by gender. Study subjects will receive the mobile app, LowSalt4Life, or usual dietary advice for 8 weeks. LowSalt4Life provides a multifaceted intervention based on just-in-time contextual tailored messages at grocery stores and restaurants. The primary endpoint is the change in the estimated 24-hour urinary excretion of sodium from spot urine. Secondary outcomes include change in the sodium content of the food frequency questionnaire, confidence in following a low-sodium diet, urine chloride and creatinine dipsticks, and blood pressure.

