### Statistical Approach

The primary endpoint this study is powered for is the estimated 24-hour urinary excretion of sodium from spot urine. Based on the data in patients with hypertension, we conservatively expect the 24-hour urinary excretion of sodium to decrease from 3400 (SD 1200) mg/24 hours to 2400 (SD 1200) mg/24 hours (35% reduction in sodium intake) in the mobile app group and a decrease from 3400 (SD 1200) mg/24 hours to 3300 (SD 1200) mg/24 hours in the usual care group [30]. The total sample size of 24 patients (12 in each group) and 32 patients (16 in each group) will provide 80% and 90% power, respectively, for a 35% reduction in sodium intake. In order to account for patients dropping out or incomplete follow-up, we are enrolling a total sample of 50 patients (25 in each group). We will use a two-sided *t* test to compare the change in each outcome over time in the mobile app group versus the usual care group. Other quantitative measures of sodium intake will be 24-hour urinary excretion of sodium and estimated 24-hour urinary excretion of sodium from chloride and creatinine dipsticks, which will be analyzed using a two-sided *t* test and repeated measures analysis of variance, respectively.

Although not powered to determine the impact, other measures of the effectiveness of this intervention will be summarized and evaluated. The percent change in confidence following a low-sodium diet will be analyzed using a two-sided *t* test. The change in blood pressure over time will be analyzed using repeated measures analysis of variance.

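### The only blood-pressure route described is entry into the app, which usual-care patients do not receive, although blood pressure is a secondary outcome for judging the app

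*Protocol article*

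**What the plan says.** **Status.** The Abstract (Methods) names the secondary outcomes, which include "confidence in following a low-sodium diet, urine chloride and creatinine dipsticks, and blood pressure".

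**Analysis.** The Statistical Approach section sets out a general aim to "compare the change in each outcome over time in the mobile app group versus the usual care group". For blood pressure it then says: "The change in blood pressure over time will be analyzed using repeated measures analysis of variance". That sentence comes in a paragraph on further indicators of the intervention's effectiveness, for which the trial is stated not to be powered.

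**Collection.** The Outcomes section describes one route: "Blood pressure will be monitored on a weekly basis by patients, and the results will be entered into the mobile app and graphically represented". The sentence closes a paragraph that is otherwise about app usage analytics, push notifications and scanned items.

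**Who has the app.** The Abstract says: "Study subjects will receive the mobile app, LowSalt4Life, or usual dietary advice for 8 weeks". General Design says: "Enrolled patients will be randomized to the mobile app or usual care in a 1:1 fashion", and: "Patients randomized to the mobile app will receive a 30-minute training session about the mobile app". No app access or app training is described for usual care.

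**Other mention.** The only other trial blood-pressure value is the exclusion limit in Study Subjects: "SBP >180 mm Hg, diastolic blood pressure >110 mm Hg".

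**The concern.** A comparison between randomised groups needs the outcome measured in the same way in both. Here the stated recording tool is the treatment itself, so following the text literally gives one of two situations:

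- **Usual care has no follow-up blood pressure.** The repeated measures analysis then describes a time trend in the app arm with no concurrent control, and says nothing about the app's effect.
- **Usual care has blood pressure by some other, undescribed route.** The arms then differ in how, when and how completely readings are captured, and that difference is mixed up with the treatment effect.

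In either case app-arm readings arrive only from patients who open the app and enter them. The article itself treats the extent of app use as something to be measured. Patients who stop using the app would also stop contributing blood pressures, so missing values would probably follow engagement. A statistical analysis plan cannot repair this, because it cannot create readings that were not collected.

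**Working it through.** The plan gives no figure to reproduce on this point. The check sets the statements side by side.

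**Step 1. Is a between-group comparison intended?** The blood-pressure sentence in Statistical Approach does not itself name the groups. However, the same section aims to compare the change in each outcome between the app and usual-care groups, and it places blood pressure among the indicators of effectiveness. A single-arm trend could not serve that purpose. So yes.

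**Step 2. Which patients does each described route reach?**

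| Outcome | Time points stated | Recording depends on the app? | App arm (25 planned) | Usual care (25 planned) |
|---|---|---|---|---|
| 24-hour dietary recall (ASA24) | weeks 0 and 8 | No (separate website) | 25 | 25 |
| 24-hour urine sodium | baseline and week 8 | No | 25 | 25 |
| Spot-urine sodium (primary) | baseline and week 8 | No | 25 | 25 |
| Chloride and creatinine dipsticks | baseline and weeks 2, 4, 6, 8 | No | 25 | 25 |
| Confidence scale (SCFLDS) | baseline and week 8 | No | 25 | 25 |
| Blood pressure | weekly | Yes | 25 | 0 described |

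The counts are the planned 50 patients at 1:1, that is 50 / 2 = 25 per group, before dropout. Blood pressure is the only outcome in this table whose stated recording route is the randomised product.

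**Step 3. What does that mean for the analysis?** Taking one reading per week for 8 weeks and no dropout, the described route would give 25 × 8 = 200 weekly readings in the app arm and 0 × 8 = 0 in usual care. The group-by-time term of a repeated measures analysis cannot be estimated when one group has no follow-up values.

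**Step 4. Could the eligibility reading fill the gap?** Applying the upper blood-pressure limits implies that a value is known at screening in both arms. It is not described as an outcome measurement, and even if used it would supply at most a pre-treatment value, not follow-up.

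**Step 5. Is this omission or a stated rule?** A condensed article may leave out detail. Here it does give a method, and that method exists in one arm only.

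**The case against.** The strongest reply is that the article does not say usual-care patients go unmeasured. General Design uses the word patients for everyone randomised, so the statement that patients monitor weekly could cover both arms, with the app clause saying only where results go. Outcomes refers the reader to Figure 2 for details; that figure is not shown in the text at hand, and a schedule of readings could be there or in the full protocol. This stands in part. A reader might infer that usual care certainly has no blood-pressure data, and the documents do not support that. What they support is that none is described. If both arms do self-monitor, the stated recording tool still exists in only one of them, so the control route remains to be specified.

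Other stronger readings also go beyond the text:

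- **That the larger trial is justified by this trial's blood-pressure result.** The Conclusions rest on urinary sodium and leave effects on blood pressure to a later study.
- **That regression to the mean would drive an apparent fall.** Entry requires diagnosed and treated hypertension, but no minimum reading; the limits are upper exclusions. Patients are not selected for a high value, so this argument is weak.
- **That graphing readings back to the patient is a flaw.** It can fairly be seen as part of the randomised package. The difficulty is the difference in measurement route, not the feedback.

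The link between missing entries and app engagement is plausible, but the documents give no data on it.

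**Conclusion.** The concern holds in this form: the text describes no blood-pressure collection for usual care, while planning to use blood pressure to judge the app against usual care. Under the described route, 25 of 50 planned patients have no follow-up readings. If an undescribed route exists, the number is smaller, but comparability of the two routes is still not established.

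This rests on two assumptions: that usual-care patients are not given the app merely as a recording tool, which the either/or allocation and the training given to the app arm support; and that Figure 2 and the full protocol do not specify a common measurement, which cannot be checked here.

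Severity is moderate. A reader might see a fault that undermines the trial, but blood pressure is one of several secondary outcomes, the article says the trial is not powered for it, and the primary spot-urine endpoint and the other urine, diet and confidence outcomes do not depend on the app. What is at risk is any between-group statement about blood pressure.

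**What to change.** 1. State how blood pressure is obtained in both arms: the same device, procedure and record, independent of the app, at the baseline and week-8 assessments that already exist for the other outcomes.
2. Base the between-group analysis on those readings, comparing week 8 between arms with adjustment for baseline, and reword the repeated measures sentence in Statistical Approach to match.
3. Label the weekly app-entered values as descriptive app-arm data, and report how many patients contribute each week.
4. If no common record exists or can be set up, report blood pressure descriptively and remove it from the between-group secondary outcomes.

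If Figure 2 or the full protocol already provides a common measurement, stating it in Outcomes and applying items 2 and 3 is enough.

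**Cost.** A small amendment and one extra measurement at two assessments. Two points are deliberately limited. A weekly log for usual care is not proposed, because it would add structured self-monitoring to the comparator; the price is that the weekly course cannot be compared between arms. And 26 of 50 patients were already enrolled when the article was written, so common readings at both time points can be assured only for the remaining 50 − 26 = 24. Those already finished among the 26 may lack comparable readings, and the report should say how many do.
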